#### Safety

Liver function (Alanine Aminotransferase, Aspartate Transaminase, Gamma-glutamyl Transferase) and other blood-based markers (e.g. creatinine) will be assessed on all participants at the outcomes assessment. More intensive metformin-specific safety assessments will be conducted on participants randomised to receive the metformin/placebo treatment: Vitamin B12; estimated glomerular filtration rate (eGFR); full blood cell count; vital signs (e.g. blood pressure, heart rate); and medical examination.

#### Other data

Other relevant data will be collected, including, e.g. self-reported demographics (e.g. month and year of birth; age; sex; ethnicity; education;), lifestyle (e.g. alcohol/tobacco consumption; leisure activities), family history of dementia, CVD, and diabetes; relevant medical history; use of concomitant medication and nutritional supplements; self-reported oral health; hearing impairment using the Hearing in Real-Life Environments validated scale and the Digit Triple Test.

### Statistics

The trial primary comparison is Self-Guided versus FINGER 2.0 multimodal intervention arm, and the trial has been powered for this purpose. Power calculations for the primary outcome are based on FINGER data. FINGER included 1260 participants (~ 33% *APOE* ε4 carriers), with an overall drop-out rate of 12% during the 2-year intervention. We estimate that a smaller sample size would be sufficient for MET-FINGER, based on (i) *APOE* ε4 enrichment at least 50% (stratified analysis of FINGER data indicated intervention benefits especially among ε4 carriers); [25] (ii) potential added benefit of metformin; and (iii) optimization of the initial FINGER lifestyle intervention. In FINGER, the observed mean 2-year change (SD) in primary outcome among *APOE* ε4 carriers was 0.10 (0.38) in the control group, and 0.19 (0.34) in the intervention group. A sample size of 506 participants would be needed to demonstrate a between-group difference with 80% power and at 5% significance level. Assuming a 15% drop-out over 2 years, a total sample size of 600 participants would be required.

The primary efficacy analysis will be based on the modified intention-to-treat population, including all randomly assigned participants with baseline and at least one post-baseline observation.

Appropriate transformation to skewed NTB components will be applied. Mixed-effects regression models with maximum likelihood estimation will be applied to analyse change in cognitive scores, as a function of randomization group, time, and group × time interaction. The site will also be included in the model as fixed effect. Non-linearity of change will be taken to account. The other secondary endpoints will be analysed using the appropriate generalised mixed-effects regression model depending on the outcome distribution.

Potential heterogeneity of intervention effects will also be investigated in subgroup analyses, for both primary and secondary outcomes by, e.g. demographics, *APOE* ε4 carrier status, baseline cognitive and functional level, and intervention adherence, although the trial is not powered for such analyses.

For most exploratory outcomes of the lifestyle + metformin trial-within-trial, the same model in the primary analysis of the trial will be used for continuous outcome variables; for categorical outcome variables (e.g. adherence-related outcomes) logistic regression models will be applied. For retention rate and target metformin dose, chi-2 test will be used to compare the three arms.

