## Methods

### Study design

MET-FINGER is a randomised, controlled, parallel-group, multicentre phase-IIb proof-of-concept clinical trial testing the FINGER 2.0 multimodal lifestyle-based intervention, including a pharmacological trial-within-trial with metformin (Fig. 2). The participants will be first randomised 1:1 to the FINGER 2.0 intervention (SMLI for all participants + metformin where appropriate; active arm) or the SGMI (regular health advice; control arm). Participants allocated to the FINGER 2.0 intervention, and with indicators T2D risk, but no diagnosed/suspected diabetes, will be randomised 1:1:1 to receive metformin 2000 mg/day, metformin 1000 mg/day, or placebo, together with the SMLI. Participants allocated to the FINGER 2.0 intervention but not eligible for metformin treatment will receive the SMLI alone. At each site, both randomisation steps (Fig. 2) are carried out using a computer-generated list from the OpenClinica database. In each randomisation step, the list is stratified by site and programmed using random blocks of various sizes.

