### Outcomes

Primary and secondary outcomes comparison will be conducted on the FINGER 2.0 multimodal intervention group (active arm) vs the SGMI group (control arm). A comparison of exploratory outcomes will be conducted among the three SMLI + metformin/placebo groups.

Table 2 presents the schedule of the outcomes’ assessment. The bibliography for validated assessment tools, tests, and scales used in the trial is presented in Supplementary Table 1.

**Table 2 Tab2:** Full schedule of outcomes assessments

Assessments	Outcomes assessment visits			
***Primary and secondary outcomes***	**Baseline**	**6 months**	**12 months**	**24 months**
Neuropsychological Test Battery (Primary outcome and secondary cognitive outcomes)	**X**		**X**	**X**
Clinical Dementia Rating Sum of Boxes (Study Partner required)	**X**		**X**	**X**
Activities of daily living	**X**		**X**	**X**
Healthy Lifestyle Index	**X**		**X**	**X**
Physical measurements (BMI, waist, waist/hip ratio, blood pressure)	**X**	**X**	**X**	**X**
Blood markers (lipid profile and glucose metabolism)	**X**	**X**	**X**	**X**
OGTT (only groups receiving metformin/placebo)	**X**		**X**	**X**
Incident cardiovascular disease	**X**		**X**	**X**
FINGER healthy diet index, nutrient and food intake	**X**		**X**	**X**
Levels of physical activity (self-reported and objectively measured)	**X**		**X**	**X**
Short Physical Performance Battery	**X**			**X**
Hand grip strength, and timed 10-m dual-task test	**X**		**X**	**X**
Center for Epidemiological Studies-Depression Scale	**X**		**X**	**X**
Perceived Stress Scale	**X**		**X**	**X**
Insomnia Severity Index	**X**		**X**	**X**
RAND36 and 15D scales for health-related quality of life	**X**		**X**	**X**
Self-reported data for utilisation of healthcare resources	**X**		**X**	**X**

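### The stated primary model makes no use of baseline cognition, so the group × time test gives away a modest amount of precision (about 1 to 5 power points)

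*Protocol article*

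**What the plan says.** The Statistics section of the protocol article sets out the primary model: "Mixed-effects regression models with maximum likelihood estimation will be applied to analyse change in cognitive scores". The terms are randomised group, time and group × time, followed by "The site will also be included in the model as fixed effect". No baseline NTB covariate, equal-baseline constraint or site × time term is named. Baseline cognitive level appears in that section only as a subgroup factor.

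In Table 2 (Outcomes), the row beginning "Neuropsychological Test Battery (Primary outcome and secondary cognitive outcomes" is marked at baseline, 12 and 24 months. Under Data collection, the baseline outcome assessment comes before the first randomisation. The modified intention-to-treat population requires a baseline and at least one later observation. Randomisation is stratified by site (Study design).

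The sample size uses 2-year changes with SDs in the original FINGER trial: "0.10 (0.38) in the control group, and 0.19 (0.34) in the intervention group". From these, "A sample size of 506 participants would be needed to demonstrate a between-group difference" "with 80% power and at 5% significance level", and then "Assuming a 15% drop-out over 2 years, a total sample size of 600 participants would be required". Allocation is equal: "The participants will be first randomised 1:1 to the FINGER 2.0 intervention".

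**The concern.** The natural reading is that baseline is one row of the response, since only then does group × time measure the effect from baseline onwards. With a free group main effect, the model lets the arms have different true baseline means, which randomisation rules out. The 24-month interaction is then essentially the difference between arms in raw change, and part of its variance comes from the chance baseline imbalance. If the response were instead change at 12 and 24 months, baseline NTB would still be absent from the model. The point about baseline therefore holds on either reading.

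A second, smaller point applies only to the natural reading. A site main effect moves all visits of a site by the same amount, so it does not adjust change for the one factor used in stratification.

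What is at stake is power. The design has little slack: 600 × 0.85 = 510 evaluable against 506 needed. A few power points that need no new data are worth having.

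**Working it through.** **Inputs from the documents.** Difference 0.19 − 0.10 = 0.09; SDs of change 0.38 and 0.34; 80% power; 5% level (two-sided assumed, as sidedness is not stated); 1:1 allocation; 15% drop-out; sites of about 300, 200 and 100.

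**Assumed.** The SD of the baseline composite and its correlation with the 24-month score are not given. I assume equal SDs at the two times and a baseline SD of 0.5 to 1.0. The upper end is a ceiling, because the components are standardised to baseline SD 1 before averaging.

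**1. The plan's own figure.** Pooled variance of change = (0.38² + 0.34²)/2 = (0.1444 + 0.1156)/2 = 0.13, so the SD is 0.3606. The normal formula gives n per arm = 2 × (1.960 + 0.842)² × 0.13/0.09² = 251.9, so 252 per arm, or 504 in total. The noncentral t gives 253 per arm, or 506, with power 0.800. This is the stated figure. Inflation gives 506/0.85 = 595.3, so 596 against the stated 600. The planned power therefore rests on unadjusted change.

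**2. Gain from baseline adjustment.** With common SD σ and correlation ρ, the variance of change is 2σ²(1 − ρ) and the baseline-adjusted variance is σ²(1 − ρ²). The ratio is (1 + ρ)/2. Setting 2σ²(1 − ρ) = 0.13 gives ρ = 1 − 0.13/(2σ²). For σ = 0.6, ρ = 1 − 0.13/0.72 = 0.82 and the ratio is 0.91.

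| Assumed baseline SD | ρ | Variance ratio | N for 80% power | Power at 506 |
|---|---|---|---|---|
| no adjustment | – | 1 | 504 | 80% |
| 0.5 | 0.74 | 0.87 | 440 | 85.3% |
| 0.6 | 0.82 | 0.91 | 460 | 83.7% |
| 0.7 | 0.87 | 0.93 | 472 | 82.8% |
| 0.8 | 0.90 | 0.95 | 480 | 82.2% |
| 1.0 | 0.935 | 0.97 | 488 | 81.4% |

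(Normal approximation throughout.) Against 504, the saving runs from 64 participants down to 16.

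**3. Check on the longitudinal model.** Random-intercept data were simulated for 510 participants with visits at 0, 12 and 24 months, site-stratified allocation and baseline SD 0.6, and analysed by generalised least squares with the covariance held at its true value.

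- Complete data: the standard error of group × time at 24 months was 0.03194, both without site and with site as a main effect, and the estimates were identical. A common baseline mean gave 0.03046. The ratio 0.03046/0.03194 = 0.954 is a fall of 4.6% in the standard error and about 9% in the variance, in line with the row for SD 0.6.
- With 15% missing at 24 months: the standard error was 0.0340 with or without the site main effect, and the estimate moved by at most 0.0008. A common baseline mean gave 0.0326, a fall of 4.1%.

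Because the covariance was held fixed, these runs cannot show what site × time would gain. That is worked out next.

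**4. Gain from site × time.** With site weights 1/2, 1/3 and 1/6 and mean changes evenly spaced over a total spread g, the share of change variance explained is R² = Var(site means)/0.13. For g = 0.20 the variance of the site means is 0.0100 − 0.0667² = 0.0056, so R² = 4.3%.

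| Assumed spread g | R² | N for 80% power | Power at 506 |
|---|---|---|---|
| 0.05 | 0.3% | 504 | 80.3% |
| 0.10 | 1.1% | 500 | 80.6% |
| 0.20 | 4.3% | 484 | 81.9% |

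**The case against.** The strongest reply has three parts.

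First, the article condenses a fuller protocol, and the analysis plan is not shown. How baseline enters and the full covariate list may be settled there. This stands as a limit on certainty. It does not remove the point, because the article states the model's terms and names one covariate, site, without baseline. If the analysis plan already adjusts for baseline, the remedy is to align the wording.

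Second, analysis and sizing agree. An unadjusted change contrast delivers the planned power, so nothing is invalid. This stands in full. A reader might infer that the trial is underpowered, biased or exposed to type I error inflation. The reproduced 506 rules out a shortfall from this cause, and an unadjusted comparison of randomised arms is not biased.

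Third, the site point is conditional and its size is unknown. If the response is change at the post-baseline visits only, the site main effect does act on the group contrast. A reader might also infer that leaving out site × time is a material loss. One can build such a case: with site mean changes shifted by ±0.2, the model standard error is about 7% too large and the type I error is 3.3%. That is a 0.4 range between extreme sites against a planned effect of 0.09, and the article reports no between-site difference in change. Even there the error is conservative. Local differences in recruitment source, language and delivery make some difference in change plausible, but not one of that size.

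**Conclusion.** The point holds as a modest efficiency loss. The stated model leaves unused a pre-randomisation measurement that every analysed participant has. Adjusting for it would lower the variance by about 3% to 13% and add about 1 to 5 power points at 506 evaluable. Those figures rest on equal SDs at baseline and 24 months, a baseline composite SD between 0.5 and 1.0, and the planning SD of change carrying over to this trial. Some gain remains whenever the correlation is below 1.

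Site × time is secondary. It matters only if baseline is a row of the response, and it is likely to add about 0 to 2 power points for an assumed spread of up to 0.20.

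**What to change.** State how baseline NTB enters the primary model, and use it in one of two ways:

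- a constrained-baseline longitudinal model, with baseline, 12 and 24 months as the response, time as categories, a common baseline mean across arms, and group × time at the two later visits; or
- a model of the 12- and 24-month scores (or changes) with baseline NTB as a covariate.

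In either case, name the 24-month group difference as the primary contrast, which matches the 2-year change used for the sample size. If baseline is a row of the response, add site × time so that the stratification factor acts on change. If it is a covariate, the site main effect already acts on the group contrast.

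The cost is wording in the analysis plan, settled before unblinded outcome data are seen. No new data are needed, no participant is lost (the primary population already requires a baseline value), and the sample size can stay at 600.

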### Data collection

Participants will be invited to a first screening visit, where basic demographics will be collected, and Study Eligibility Criteria (Table 1) will be assessed. Eligible participants will be invited to the baseline visit, where all outcome measures will be assessed prior to the first randomisation step (FINGER 2.0 intervention or SMGI). Participants randomised to the FINGER 2.0 group will start receiving the SMLI and will be further assessed for the Metformin Eligibility Criteria using baseline data and additional assessments at a second screening visit where metformin eligibility assessments will be completed (Table 1). Eligible participants will undergo the second randomisation step, and treatment will be initiated.

All participants will be invited to three additional outcome assessments, where basic safety assessments will be also conducted. At 6 months, a subset of outcomes related to blood sample collection, physical measurements, and health status will be assessed. At 12 and 24 months (end of study) a full outcomes assessment will be conducted, with additional data collection on trial participation adherence and feedback.

Participants randomised to the metformin/placebo treatment will undergo additional safety assessments, every 2 weeks until the full dose is established, and every 3 months after that.

Nominating a study partner to provide information for the assessment of the Clinical Dementia Rating scale Sum of Boxes (CDR-SB) [23] will be supported, but not mandatory.

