***Exploratory outcomes***				
Healthy lifestyle changes, e.g. exercise, diet, cardiovascular/metabolic factors and biomarkers, and cognitive activity	**X**		**X**	**X**
AD-related blood biomarkers	**X**	**X**	**X**	**X**
Neuroimaging (Planning phase)	**X**			**X**
Retention rate	Continuously during the study			
Adherence to the SMLI and its individual components	Continuously during the study based on participation to the SMLI structured activities			
Target metformin dose	Continuously during the study with compliance to treatment assessed at each dispensing appointment (every 3 months)			

The bibliography for assessment tools, tests, and scales used in the trial is presented in Supplementary Table 1

*AD* Alzheimer’s disease, *BMI* body mass index, *FINGER* Finnish Geriatric Intervention Study to Prevent Cognitive Impairment and Disability, *OGTT* oral glucose tolerance test, *SMLI* Structured Multimodal Lifestyle Intervention

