Temporary interruptions will be implemented prior to elective major surgery or other medical procedures as required by the treating physician (e.g. CT scan with contrast infusion), and will be reinstated only after normal renal function is reported. Regardless of the final dose achieved or treatment discontinuation, participants will continue receiving the SMLI. A pre-defined procedure for treatment allocation unblinding will be conducted by an authorised study physician, if required for medical reasons and to ensure participant safety.

Adherence to the study-drug treatment is monitored at each dispensing appointment (i.e. every 3 months) by cross-checking the number of tablets left from the previous dispensing against the number of tablets that should have been left if the participant had fully adhered to the treatment. The assessor will also examine the study-drug diary that participants receive at each dispensing appointment, which includes detailed instructions for the tablets to be taken daily, and allows to record the actual number of tablets taken.

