#### Self-Guided Multimodal Lifestyle Intervention (SGMI)

During the outcomes assessment visits (baseline, 6, 12 and 24 months), the control group will receive general, non-tailored, health advice to independently implement healthy lifestyle changes as part of their daily routine. Like in the SMLI, participants in this group will receive the results and explanation of their blood tests; referral/advice to seek medical care will be also provided, if needed. After Randomisation 1 (Fig. 2) is completed, and regardless of group allocation, all participants will receive three educational leaflets providing generic recommendations related to *diet/nutrition*, *physical activity*, and *cardiovascular/metabolic risk factors for dementia*, with content based on local/national guidelines.

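### Intervention adherence is listed as a subgroup factor for the FINGER 2.0 versus SGMI effect, but it arises after randomisation and only in the active arm, so it cannot define a randomised subgroup

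*Protocol article*

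**What the plan says.** The subgroup plan is in the Statistics section of the protocol article: "Potential heterogeneity of intervention effects will also be investigated in subgroup analyses, for both primary and secondary outcomes by" a list of examples. The list opens with demographics and APOE ε4 carrier status and ends with "baseline cognitive and functional level, and intervention adherence, although the trial is not powered for such analyses". The Outcomes section fixes the contrast that these effects refer to: "Primary and secondary outcomes comparison will be conducted on the FINGER 2.0 multimodal intervention group (active arm) vs the SGMI group (control arm").

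Adherence is described in several places:

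- Lifestyle programme (Table 2, exploratory outcomes): "Continuously during the study based on participation to the SMLI structured activities".
- Physical activity: resistance and balance training is self-recorded in a participant diary (Intervention, SMLI).
- Study drug (Metformin/placebo treatment): "Adherence to the study-drug treatment is monitored at each dispensing appointment (i.e. every 3 months"), by tablet count and diary.
- All participants (Data collection): the 12- and 24-month assessments come "with additional data collection on trial participation adherence and feedback".

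On the comparator, the SGMI section says that "the control group will receive general, non-tailored, health advice to independently implement healthy lifestyle changes as part of their daily routine". It describes no structured sessions for controls to attend.

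**The concern.** A subgroup analysis of a randomised effect asks whether the active-minus-control difference varies across levels of a factor. For randomisation to protect each within-level difference, the factor must exist in both arms and must not be affected by allocation. Demographics, genotype and baseline cognition meet these conditions. Adherence meets neither, yet it stands in the same sentence on the same footing.

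A selected part of the active arm would then be compared with controls who have not been selected in the same way. Anything that drives both attendance and cognitive change would appear as a treatment effect. Cognitive decline that causes people to stop attending would appear as a lack of effect in non-adherers.

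The Limitations section says that the trial's findings will inform phase III selection criteria, dose selection and power calculations. An adherence gradient reported as effect modification could therefore carry into later design decisions.

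**Working it through.** **1. Is there an adherence measure in both arms?**

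| Measure | When | Who has it |
|---|---|---|
| Participation in SMLI activities | during follow-up | active arm only |
| Exercise diary | during follow-up | active arm only |
| Tablet count and drug diary | every 3 months once on treatment | metformin/placebo groups only, all within the active arm |
| Trial participation adherence | 12 and 24 months | all participants |

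Only the last row covers controls. It concerns taking part in the trial, not adherence to an intervention, so it does not fill the gap. Every measure is taken after the first randomisation.

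**2. Could adherence depend on the participant's course?** The article gives reasons to think so. Study drug is reduced for poor tolerance and stopped for related adverse events, new diabetes or reduced renal function. The lifestyle arm includes at least 144 web-based cognitive sessions of rising difficulty. That declining participants complete fewer of them is plausible, but this is an inference and the article does not state it.

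**3. The plan's own figures.** In APOE ε4 carriers in FINGER, 2-year change (SD) was 0.10 (0.38) in controls and 0.19 (0.34) in the intervention group.

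- Difference: 0.19 − 0.10 = 0.09.
- Pooled SD: √((0.38² + 0.34²)/2) = √0.13 = 0.3606.
- n per arm, 80% power, two-sided 5% (the article does not state sidedness): 2 × (1.960 + 0.842)² × 0.13 / 0.09² ≈ 252, or 504 in total. The t-test version gives 253 per arm, or 506, which is the stated figure.
- With 15% drop-out: 506/0.85 = 596, rounded in the plan to 600.

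None of this depends on the adherence analysis.

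**4. How large could the distortion be?** The article gives neither a split rule nor a correlation, so both are assumed here. Split the active arm at median adherence, let r be the correlation between adherence and 2-year change that is not due to treatment, and set the true effect to zero. With approximate normality, the upper half exceeds the arm mean by r × φ(0)/0.5 = 0.798r standard deviations. The spurious difference from controls is therefore

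b = 0.798 × r × 0.3606 = 0.288r.

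For the false-positive rate, take 600 × 0.85 / 2 = 255 evaluable per arm, so about 127 adherers against 255 controls. Then SE = 0.3606 × √(1/127 + 1/255) = 0.0392. For adherers against non-adherers, the difference is 2b with SE = 0.3606 × √(1/127 + 1/128) = 0.0452.

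| Assumed r | Adherers − controls (b) | As % of 0.09 | False-positive rate, adherers v controls | Adherers − non-adherers (2b) | False-positive rate, adherers v non-adherers |
|---|---|---|---|---|---|
| 0 | 0 | 0% | 5% | 0 | 5% |
| 0.1 | 0.029 | 32% | 11% | 0.058 | 25% |
| 0.2 | 0.058 | 64% | 31% | 0.115 | 72% |
| 0.3 | 0.086 | 96% | 60% | 0.173 | 97% |

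If the true effect were a uniform 0.09, r = 0.3 would give about 0.09 + 0.086 = 0.176 in adherers and 0.09 − 0.086 = 0.004 in non-adherers: strong apparent heterogeneity where there is none.

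**The case against.** The strongest defence is that the article does not say how adherence would enter the analysis. The list is introduced as examples, and a fuller protocol or analysis plan may specify a within-arm dose-response or a complier-average estimate. Either could be called heterogeneity by adherence. This stands as far as it goes: a reader might infer that adherers against all controls is the only contrast the plan allows, and the text does not support that. It does not remove the point, because the article names adherence as a subgroup factor beside baseline variables for a between-arm effect, and further detail cannot make it a valid one.

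A reader might also infer that adherers are fitter or cognitively better to begin with, so that the analysis is almost certain to show a larger effect in them. The documents say neither. The primary outcome is change in the test battery, so a better starting level does not by itself produce a larger change. What matters is the link between adherence and change. The article does not report that link, and if it is zero there is no bias.

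Finally, the analysis is supportive and already flagged as unpowered. That limits the consequence. It does not answer the point, because low power concerns random error, and a larger sample would only make a biased contrast look more convincing.

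**Conclusion.** The concern holds as a fault in the subgroup specification. Adherence as described is measured after randomisation and only in the active arm, so it cannot define a subgroup of the randomised comparison. A contrast of adherers with controls is open to confounding and reverse causation.

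The size is unknown. The range of 0 to 0.086, against the planned 0.09, rests on assumed correlations of 0 to 0.3, a median split, approximate normality and no true effect. It shows that a modest correlation would be enough to matter, not what will happen in this trial.

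No confirmatory conclusion is at risk. The primary analysis uses the modified intention-to-treat population, which is not selected on adherence, and 506/600 is unchanged. The correction is worth making but does not threaten the trial's main result.

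**What to change.** - Remove intervention adherence from the subgroup list. Restrict subgroups to variables fixed before the first randomisation, each tested by a group × time × subgroup interaction in the planned mixed model.
- Report adherence in a separate analysis labelled as non-randomised, in one of two forms. One is a descriptive association within the active arm. The other is a complier-average or principal-stratum estimate with its assumptions stated and results shown across several attendance thresholds.

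For the second form, the critical assumption is that attendance below the threshold has no effect. This is doubtful in a tailored, multi-component programme, where people below any threshold still receive part of the intervention. In the simple instrumental-variable form, the between-arm difference and its standard error are both divided by the proportion above the threshold, so the estimate is less precise. Any benefit to people below the threshold is wrongly credited to those above it.

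The cost is one phrase removed and one supporting analysis described. The article estimates study completion in February 2027 and the primary analysis in September 2029, so on its own dates the change can be made before analysis.
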